# A multi-center interventional study to assess pharmacokinetics, effectiveness, and tolerability of prolonged-release tacrolimus after pediatric kidney transplantation: study protocol for a prospective, open-label, randomized, two-phase, two-sequence, single dose, crossover, phase III b trial

**DOI:** 10.3389/fneph.2024.1331510

**Published:** 2024-02-20

**Keywords:** tacrolimus, Prograf^®^, Envarsus^®^, pharmacokinetics, pharmacodynamics, pharmacogenetics, adherence, kidney transplantation

## Abstract

**Background:**

Tacrolimus, a calcineurin inhibitor (CNI), is currently the first-line immunosuppressive agent in kidney transplantation. The therapeutic index of tacrolimus is narrow due to due to the substantial impact of minor variations in drug concentration or exposure on clinical outcomes (i.e., nephrotoxicity), and it has a highly variable intra- and inter-individual bioavailability. Non-adherence to immunosuppressants is associated with rejection after kidney transplantation, which is the main cause of long-term graft loss. Once-daily formulations have been shown to significantly improve adherence compared to twice-daily dosing. Envarsus^®^, the once-daily prolonged-release formulation of tacrolimus, offers the same therapeutic efficacy as the conventional twice-daily immediate-release tacrolimus formulation (Prograf^®^) with improved bioavailability, a more consistent pharmacokinetic profile, and a reduced peak to trough, which may reduce CNI-related toxicity. Envarsus^®^ has been approved as an immunosuppressive therapy in adults following kidney or liver transplantation but has not yet been approved in children. The objective of this study is to evaluate the pharmacokinetic profile, efficacy, and tolerability of Envarsus^®^ in children and adolescents aged ≥ 8 and ≤ 18 years to assess its potential role as an additional option for immunosuppressive therapy in children after kidney transplantation.

**Methods/design:**

The study is designed as a randomized, prospective crossover trial. Each patient undergoes two treatment sequences: sequence 1 includes 4 weeks of Envarsus^®^ and sequence 2 includes 4 weeks of Prograf^®^. Patients are randomized to either group A (sequence 1, followed by sequence 2) or group B (sequence 2, followed by sequence 1). The primary objective is to assess equivalency between total exposure (of tacrolimus area under the curve concentration (AUC0-24)), immediate-release tacrolimus (Prograf^®^) therapy, and prolonged-release tacrolimus (Envarsus^®^) using a daily dose conversion factor of 0.7 for prolonged- versus immediate-release tacrolimus. Secondary objectives are the assessment of pharmacodynamics, pharmacogenetics, adherence, gut microbiome analyses, adverse events (including tacrolimus toxicity and biopsy-proven rejections), biopsy-proven rejections, difference in estimated glomerular filtration rate (eGFR), and occurrence of donor-specific antibodies (DSAs).

**Discussion:**

This study will test the hypothesis that once-daily prolonged-release tacrolimus (Envarsus^®^) is bioequivalent to twice-daily intermediate-release tacrolimus after pediatric kidney transplantation and may reduce toxicity and facilitate medication adherence. This novel concept may optimize immunosuppressive therapy for more stable graft function and increased graft survival by avoiding T-cell mediated and/or antibody-mediated rejection due to improved adherence. In addition, the study will provide data on the pharmacodynamics and pharmacogenetics of prolonged-release tacrolimus in children and adolescents.

**Clinical Trial Registration:**

EUDRA-CT 2019-003710-13 and ClinicalTrial.gov, identifier NCT06057545.

## Introduction

From the first successful kidney transplant in 1954 to the current era of transplantation, there have been tremendous developments in transplant immunology and immunosuppressive therapy. Tacrolimus, a calcineurin inhibitor (CNI), is currently the first-line immunosuppressive agent in kidney transplantation. In children, the start dose of tacrolimus is conventionally determined based on body surface area or weight. Further dosing depends on monitoring of tacrolimus trough levels in blood. Non-adherence to immunosuppressants is associated with the development of T-cell-mediated and/or antibody-mediated rejection after kidney transplantation, which is the major cause of long-term graft loss. The therapeutic index of tacrolimus is narrow. The main goal is to reach/maintain the target blood concentration of tacrolimus without the risk of graft rejection or toxicity. It has already been shown that once-daily, rather than twice-daily drug formulations lead to a significant improvement in adherence (1). Therefore, it is expected that prolonged-release tacrolimus would lead to a more stable tacrolimus exposure and thereby provide a more reliable immunosuppression after kidney transplantation.

The once-daily formulation of tacrolimus (extended-release tacrolimus), Advagraf^®^, was designed to reduce the burden of daily pills compared to twice-daily Prograf^®^. A pediatric study has demonstrated comparable pharmacokinetics when immediate-release tacrolimus was converted to the prolonged-release formulation. The conversion was effective and well tolerated (2). Recently, a new prolonged-release tablet formulation of tacrolimus (Envarsus^®^) using MeltDose™ (US Patent No. 7,217,431), a drug delivery technology that enhances the absorption of fat-soluble drugs, was approved as an immunosuppressive medication after kidney and liver transplantation in adults, but it has not yet obtained approval in children (3). Studies in adults have shown that Envarsus^®^ provides the same therapeutic efficacy as the conventional immediate-release formulation of tacrolimus (Prograf^®^) with improved bioavailability, a more consistent pharmacokinetic profile, and a reduced peak-to-trough profile, which may result in reduced CNI-related toxicity.

In recent years, different protocols combining different immunosuppressive agents have been used in pediatric kidney transplantation with changes over time and large variability between centers and countries (4). The choice of the immunosuppressive regimen is based on efficacy trials as well as personal expertise. Patient stratification to immunosuppressants has rarely been based on the risk of viral infection or metabolic disease but is often tailored to the individual immunologic risk of rejection. To summarize the few randomized pediatric trials on immunosuppression, tacrolimus appears to have advantages over cyclosporine A in pediatric kidney transplantation, steroid-free protocols are feasible in low-immunologic risk, and induction therapy with interleukin-2 (IL-2) receptor antagonists may not be beneficial in a standard-risk population (5). It is therefore important to find the best combination of immunosuppressive agents that optimizes allograft survival by preventing acute rejection while limiting agent toxicities (6).

The inter-individual differences in tacrolimus exposure in pediatric patients are related to patient characteristics, such as weight, age, and laboratory parameters such as hematocrit (Hct), concomitant medications, and pharmacogenetic diversity of the CYP3A4/A5 genes (7). As for intra-patient variability, several factors have been identified, including interactions with concomitant medications and food, diarrhea, and interchangeable administration of generic tacrolimus formulations. There is a wide range of tacrolimus intra-patient variability in adult and pediatric populations from < 5 to > 50%, with average values of 15–30% (7, 8). It needs to be recognized that high tacrolimus intra-patient variability is an important prognostic risk factor after solid organ transplantation (7, 8).

Data on the pharmacokinetics of immediate-release tacrolimus versus prolonged-release tacrolimus in the pediatric population are scarce and not available for immediate-release tacrolimus versus extended-release LCT-tacrolimus. Vondrak et al. showed a 1.3 to 1.9 increase in tacrolimus Tmax for prolonged-release tacrolimus versus immediate-release tacrolimus in pediatric solid organ transplant recipients (9). The main finding of this study was that systemic exposure (AUC0-24) was lower for the early post‐transplant period for the prolonged‐release formulation which equalized by 1 month after transplantation. These findings were consistent with those reported in *de novo* adult transplant recipients (9, 10). In adult transplant recipients, the switch from immediate-release tacrolimus to extended-release LCPT tacrolimus was safe and resulted in a 12.5% to 16% increase in the tacrolimus trough level over total daily dose ratio, indicating improved bioavailability (11, 12). Despite the finding that tacrolimus trough levels remained within the standard reference range for most patients (11), the coefficient of variation for the intra-patient variability did not change significantly after the switch from immediate-release tacrolimus to extended-release LCP tacrolimus (13).

The objective of this study is to evaluate the pharmacokinetic profile, efficacy, and tolerability of Envarsus^®^ in children and adolescents aged ≥ 8 and ≤ 18 years to assess its potential role as an additional option for immunosuppressive therapy after pediatric kidney transplantation.

## Methods/Study design

The study is designed as a randomized, prospective crossover trial. Patients receive two treatment sequences. Sequence 1 includes 4 weeks Envarsus**
^®^
** and sequence 2 includes 4 weeks Prograf**
^®^
**. A daily dose conversion factor of 0.7 for prolonged- versus immediate-release tacrolimus is used. Patients are randomized to either group A (sequence 1, followed by sequence 2) or group B (sequence 2, followed by sequence 1) with a wash-out period of 4 days between the two sequences. The trial design is summarized in **Figure 1**. The total study duration per patient (including the build-up periods) is approximately 9 weeks from visit 1. Risks and burdens for study participants have been minimized so that participation in the study over the planned 9-week duration will not exceed routine burdens. The total study duration (first patient first visit: FPFV to last patient last visit: LPLV) will be approximately 20 months, including a recruitment period of approximately 18 months.

**Figure 1 f1:**
[figure not shown]
Study design. Sequence 1: 4 weeks Envarsus^®^. Sequence 2: 4 weeks Prograf^®^. The exact timepoints of study visits are given in **Table 2**. At the beginning of the washout period, the medication administered in the first treatment sequence is discontinued and the other medication is started so that a stable build-up is secured.

The primary objective is to assess whether the tacrolimus area under the curve (AUC0-24) concentration in blood samples collected before and 1.5, 2.0, 4.0, 6.0, 8.0, 12.0, 13.5, 14.0, 16.0, 20.0, and 24.0 hours after administration in compliant patients without any protocol deviations is bioequivalent between twice-daily immediate-release tacrolimus (Prograf^®^) therapy and once-daily prolonged-release tacrolimus (Envarsus^®^) therapy using a daily dose conversion factor of 0.7 for prolonged- versus immediate-release tacrolimus. Envarsus^®^ is available in 0.75, 1.00, and 4.00 mg capsules.

A fast and easy-to-use liquid chromatography-tandem mass spectrometry (LC-MS/MS) method for the determination and quantification of tacrolimus in whole blood was developed and validated. The used method was based on an already published work for the determination of immunosuppressants in serum and plasma (7). Modifications consisted of the use of a different biological matrix (whole blood) with sample preparation and an extraction protocol of commercially available standards and control samples. Sample preparation was based on protein precipitation. A volume of 100µL of whole blood was admixed with 200µL of isotopically labeled internal standard and 200µL zinc sulfate heptahydrate, shaken on a Vortex mixer for 30sec., and pre-dispersed using an external ultrasonic bath for 10min at room temperature, with subsequent centrifugation at 4 000 × g for 15 minutes at 6°C. The analytical performance data of the assay is as follows: Recovery rate: Tacrolimus: 97.9% (2.00 µg/L) and 103% (20.00µg/L); lower limit of quantification (LLOQ in µg/L): 0.56 µg/L tacrolimus; upper limit of quantification (ULOQ in µg/L): 100.0 µg/L tacrolimus. Precision (intra-day-assay): analyte CV in % (at a concentration in µg/L), n=10 per conc.-level: Tacrolimus 3.5 (2.6); 3.4 (7.3); 2.5 (16.7); 1.6 (34.2). Precision (inter-day-assay): analyte CV in % (at a concentration in µg/L), n=10 per conc.-level: Tacrolimus 5.5 (2.6); 3.8 (7.3); 3.7 (16.7);.6 (34.2).

Secondary objectives are to assess Tacrolimus Cmax, efficacy (pharmacodynamics) in terms of residual expression of nuclear factor of activated T-cell (NFAT)-regulated gene expression, potential influence of pharmacogenetics, trough levels and doses of immediate-release tacrolimus (Prograf^®^) compared to prolonged-release tacrolimus (Envarsus^®^), cumulative tacrolimus dose, adherence, adverse events (including tacrolimus toxicity and biopsy-proven rejections), biopsy-proven rejections, differences in estimated glomerular filtration rate (eGFR) (Chronic Kidney Disease in Children (CKiD) formula) from baseline, microbiome analyses, and occurrence of donor-specific antibodies (DSA).

To determine the contribution of genetic factors for interindividual pharmacokinetic variability of tacrolimus exposure observed during the study, genetic variants in *CYP3A5*, *CYP3A4*, and *ABCB1* will be assessed in all children.

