**Inclusion Criteria**
1. Pediatric kidney transplant recipients (single-organ recipients).
2. Aged ≥ 8 years but ≤ 18 years who are receiving tacrolimus (Prograf^®^) therapy and who are able to swallow tablets with a minimum dose of 0.75 mg/day Envarsus^®^.
3. At least 6 months after transplantation.
4. Stable kidney function (delta eGFR < 10 ml/min/1.73 m^2^ (CKiD formula) over the last 3 months.
5. Women of childbearing potential who are practicing complete abstinence from sexual intercourse (periodic abstinence and withdrawal are not acceptable) or who have a sexual relationship with female partners only and/or with sterile male partners; or women of childbearing potential who are sexually active with a fertile male partner, who have a negative pregnancy test during screening and who agree to use reliable methods of contraception from the time of screening, during the study and for a period of 4 weeks following the last administration of study medication; or women without childbearing potential defined as females before menarche or at least 6 weeks after surgical sterilization by bilateral tubal ligation or bilateral oophorectomy or hysterectomy or uterine agenesis.
6. Patient/parents/legal guardian(s) must be capable of understanding the purpose and risks of the study.
7. Signed informed consent was obtained by the patient and parents/legal guardians.

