**Exclusion Criteria**
1. Coefficient of variation of tacrolimus trough levels > 0.35 over the previous 6 months.
2. Pregnancy/breastfeeding.
3. Unstable kidney function.
4. Hypersensitivity to any of the components of the medications used.
5. Not eligible for any reason according to the investigator’s evaluation.
6. Known positive HIV-1 or HCV test.
7. Participation in another clinical trial (other investigational drugs or devices at the time of enrollment or within 30 days prior to enrollment).

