### Statistical methods

The primary objective of the study is to demonstrate the equivalency between total exposure and trough levels of both Prograf^®^ and Envarsus^®^ (with a daily dose conversion factor of 0.7) in compliant patients without any protocol deviations. Therefore, the primary endpoint is the full AUC0-24 of tacrolimus levels over 24 hours. The objective is to demonstrate that the 90% confidence interval for the ratio of the full AUC0-24 of Envarsus^®^ (with a conversion factor of 0.7 for the daily dose) to Prograf^®^ is within the acceptance interval of 0.8 - 1.25 (33). This interval has been chosen in accordance with the German Federal Institute for Drugs and Medical Devices. As a secondary analysis, whether the confidence interval is also within the narrower interval of 0.9 to 1.11 recommended for drugs with a narrow therapeutic index (NTI) will be checked (33).

Demographic and baseline characteristics will be summarized as absolute and relative frequencies (for categorical outcomes), median and interquartile ranges (IQR), or arithmetic means and standard deviation. Pharmacokinetic measures will be summarized as median, geometric mean, arithmetic mean and standard deviation, minimum and maximum, and coefficient of variation. The primary endpoint – full AUC0-24 – will be calculated from tacrolimus measurements after administration of the respective medication by linear interpolation between measurement time points (see **Supplementary Material**). It will then be analyzed using an ANOVA model on the log-transformed AUC0-24 values comparing Prograf^®^ and Envarsus^®^ with sequence, subject within sequence, and period as further fixed factors as suggested by the EMA guideline (33). A summary of the assessment of the primary objective in terms of the estimand framework is given in the **Supplementary Material**.

In addition to full AUC0-24 analysis, the following pharmacokinetic parameters will form part of the evaluation: C_0_, C_max_, t_max_, and their corresponding coefficients of variation. Pharmacokinetic half-life and apparent clearance after oral administration of Envarsus^®^ and Prograf^®^ will be evaluated accordingly. Pearson’s correlation coefficients will be used to assess suitability and trough levels and AUC0-24 will be correlated.

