Low NFAT expression indicates high immunosuppression and high NFAT expression indicates low immunosuppression. The tacrolimus effect is therefore complementary to the NFAT transcripts (E=1-NFAT%). The residual NFAT expression at each time point will be compared to the corresponding tacrolimus blood concentration to estimate the peak (E_peak_) and trough (E_trough_) effect. With the help of the sigmoid E_max_ model, the immunosuppressive effect will be estimated as the percentage of E_max_ (E=%E_max_).

A test for univariate associations between changes in the gut microbial abundance profile will be performed during the switch from Prograf^®^ to Envarsus^®^ compared to changes during the pre- and post-switch time intervals (Wilcoxon test). We will also include Prograf^®^ AUC0-24 and *CYP3A* genotypes as additional predictors in these models to quantify whether microbial AUC0-24 predictors are consistent or different between Prograf^®^ and Envarsus^®^ AUC0-24 and the extent to which gut bacterial drug metabolism is independent of host metabolism. We will attempt to identify gut microbial correlates of adverse events and rejection, but the analyses will be exploratory.

All persons performing the analyses will be blinded to the sequence order. The statistical analysis plan, in which all planned analyses are described in detail, is finalized before the database lock.

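### Genotype and microbiome predictor models are framed on AUC0-24 without dose, although doses were set by trough; clearance effects shared by both formulations are then weakened by an unknown amount

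*Protocol article*

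**What the plan says.** **Outcome of the predictor analyses.** In Methods/Study design, after the secondary objectives, the pharmacogenetic aim is "To determine the contribution of genetic factors for interindividual pharmacokinetic variability of tacrolimus exposure observed during the study"; variants in CYP3A5, CYP3A4 and ABCB1 are to be assessed in all children. The Statistical methods section adds Prograf AUC0-24 and CYP3A "genotypes as additional predictors in these models to quantify whether microbial AUC0-24 predictors are consistent or different between" the two formulations. It also wants these models to show how far bacterial drug metabolism is independent of host metabolism. Dose is mentioned in neither place.

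**How dose came about.** The Introduction states "Further dosing depends on monitoring of tacrolimus trough levels in blood" and "The main goal is to reach/maintain the target blood concentration of tacrolimus without the risk of graft rejection or toxicity". Table 1 requires "At least 6 months after transplantation" on Prograf, and excludes children with "Coefficient of variation of tacrolimus trough levels > 0.35 over the previous 6 months". The Envarsus daily dose is tied to the Prograf dose by the factor 0.7. The Study drugs section says that trough is a good guide to exposure, though only for Envarsus.

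**What is already planned.** Statistical methods lists "Pharmacokinetic half-life and apparent clearance after oral administration of Envarsus" and Prograf. Doses and cumulative dose are among the secondary objectives. The article does not connect any of these to the genotype or microbiome models.

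**The concern.** In a trough-guided population, dose carries information about clearance. A child who clears tacrolimus quickly, through CYP3A genotype or drug-degrading bacteria, will tend to have been moved to a larger dose, which pulls AUC0-24 back towards the common target. The difference that the predictor analyses look for then sits partly in the dose and only partly in AUC0-24.

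At stake is how a null result is read. The Introduction attributes between-patient differences partly to CYP3A4/A5, and the Study drugs section says gut bacterial metabolism may be crucial. A weak or absent association with raw AUC0-24 would say little about either, yet could be taken as evidence against both.

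**Working it through.** The article gives no effect size, power or sample size for these analyses, so there is no figure to reproduce.

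**Step 1: algebra.** For one child and one formulation,

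log AUC = log dose − log(CL/F).

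Let log dose = c + k·log(CL/F) + scatter, where k = 0 means no titration to clearance and k = 1 complete titration. Then

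log AUC = c − (1 − k)·log(CL/F) + scatter.

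A clearance ratio R between genotype groups shows in raw AUC0-24 as R^-(1−k). In dose/AUC0-24 it shows as R, whatever k is.

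| k | AUC ratio, R = 1.5 | AUC ratio, R = 2 |
|---|---|---|
| 0 | 1.5^-1 = 0.67 | 2^-1 = 0.50 |
| 0.5 | 1.5^-0.5 = 0.82 | 2^-0.5 = 0.71 |
| 0.6 | 1.5^-0.4 = 0.85 | 2^-0.4 = 0.76 |
| 0.8 | 1.5^-0.2 = 0.92 | 2^-0.2 = 0.87 |
| 1 | 1.00 | 1.00 |

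**Step 2: power.** From the article: n = 27 (Sample size calculation). Assumed, because the article does not give them: residual between-child SD of log CL/F 0.40, occasion SD 0.20, dose scatter SD 0.15, 15 to 30% carriers, and k. The test is a two-sample t-test on the log scale, two-sided 5%. Ranges run over the carrier share.

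| k | Raw AUC0-24, R = 1.5 | Raw AUC0-24, R = 2 |
|---|---|---|
| 0 | 0.32–0.51 | 0.74–0.91 |
| 0.5 | 0.20–0.31 | 0.47–0.69 |
| 0.6 | 0.16–0.24 | 0.38–0.56 |
| 0.8 | 0.09–0.12 | 0.16–0.23 |
| 1 | about 0.05 | about 0.05 |

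On CL/F, power does not depend on k: about 0.35–0.57 for R = 1.5 and about 0.8–0.94 for R = 2. Repeat runs differ by about 0.01 to 0.02.

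**Step 3: other assumptions.** With residual SD 0.35, within-child SD 0.303 (the figure in the sample size section) and 10 to 30% carriers, power for R = 2 is 0.64–0.94 on CL/F. On raw AUC0-24 it is 0.62–0.91 at k = 0, 0.30–0.57 at k = 0.5, 0.09–0.15 at k = 0.8 and about 0.05 at k = 1. The pattern is the same.

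**Step 4: does Prograf AUC0-24 as a predictor solve it?** It depends on the question.

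- *Effects that differ between formulations.* With the fixed factor, log(AUC Envarsus/AUC Prograf) = log 0.7 − log(CL/F Envarsus) + log(CL/F Prograf). The dose cancels. A 1.5-fold formulation-specific effect with 20% carriers was recovered as 1.50, with power 0.44 at k = 0 and 0.47 at k = 1 (Step 3 assumptions). These effects are protected.
- *Clearance shared by both formulations.* Prograf AUC0-24 carries the same shared clearance as Envarsus AUC0-24, so conditioning on it removes most of what is sought. A shared 2-fold effect appears as a ratio of 0.87 to 1.00, with power 0.04 to 0.19 at every k, including k = 0 (Step 2 assumptions). This model therefore does not answer how far bacterial metabolism is independent of host metabolism.

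**The case against.** Five points can be made for the plan.

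1. *This is detail for the statistical analysis plan.* The pharmacogenetic sentence is an aim without a model or test, and the article defers detail to a plan that is not shown. This stands in part: no reader can say that genotype will be tested on raw AUC0-24 only. But the microbiome and CYP3A text does name AUC0-24 as the quantity predicted, so the article points to a particular outcome and is not merely silent.
2. *The dose-corrected quantity is already planned.* This is true of apparent clearance and the recorded doses. A reader might infer that real effects would be reported as absent. The documents do not support that, because the right outcome is available. It is only not tied to these analyses.
3. *Titration may be incomplete.* The article gives no numeric trough target and no rule for dose changes during the study, and the Introduction's remark on dosing is general background. A reader might infer that the signal is largely cancelled. That needs k of roughly 0.8 or more, which the documents cannot establish.
4. *Much of the microbiome work is unaffected.* The Wilcoxon comparison concerns within-patient changes in bacterial abundance, which titration does not enter. Formulation-specific effects survive under the 0.7 factor, provided doses are not altered separately in each period. Both points stand and limit the concern to clearance shared by the two formulations.
5. *CL/F does not make the study well powered.* For a 1.5-fold effect it reaches only about 0.35 to 0.57. This is correct, and a null result would need cautious wording either way. Even so, CL/F was no worse than raw AUC0-24 at any k examined.

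**Conclusion.** The concern holds in a limited form. AUC0-24 without dose is the named outcome for the microbiome and CYP3A predictor models, and exposure without dose is the stated target of the pharmacogenetic aim. In children dosed by trough for months, that is a poor outcome for finding drivers of clearance common to both formulations. The direction follows from algebra: attenuation towards no effect for any k between 0 and 1.

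The size rests on k, the standard deviations and the carrier share, none of which the article gives. The loss for a 2-fold effect is negligible at k = 0, moderate at k = 0.5 to 0.6, and near total at k = 0.8 to 1. The advantage of CL/F does not depend on knowing k. Only secondary analyses are touched; the primary equivalence test on AUC0-24 is unaffected.

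**What to change.** - **Genotype and between-patient microbiome models** (secondary objectives and Statistical methods): name log(CL/F) = log(actual daily dose/AUC0-24), per formulation, as the outcome. Log AUC0-24 with log dose as a covariate is an acceptable alternative. Host and bacterial contributions should be separated in this model, without Prograf AUC0-24 as a covariate.
- **Whether predictors differ between formulations:** use the within-patient log ratio of dose-normalised Envarsus to Prograf AUC0-24 as outcome, with genotype or taxon as predictor. Under an exact 0.7 factor the normalisation only adds a constant. Using actual doses covers any departure from that factor.
- **Optional:** adjust for log body weight, which is recorded at each visit.
- **Leave unchanged:** raw AUC0-24 for the primary equivalence analysis.

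The cost is one or two sentences in the protocol or statistical analysis plan before database lock. Dose, weight and AUC0-24 are already collected and apparent clearance is already a planned parameter, so conduct and sample size do not change.
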